### Patient and public involvement

While patients or the public were not directly involved in the drafting of this specific study protocol, the study’s core components are founded on patient-centered principles. The comfort cart intervention is adapted from the work of Lichen et al. (2021), which was developed to address needs identified by older adults and included the patient’s voice in the selection of the items for the comfort cart. Furthermore, the primary patient experience outcome measures are adapted from the questionnaire developed by McCusker et al. (2018), which was created through direct qualitative interviews with older adults about their emergency department experiences. We will disseminate the study findings to patient communities and participants upon completion of the research.

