### Objectives

#### Primary objective.

Evaluate the impact of implementing a comfort menu and cart on the experience of older patients treated in the ED.

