#### Sample size calculation.

The sample size calculation was based on the study by Lichen et al. (2021), which reported a difference of 0.98 on a Likert scale (ranging from 1 to 6) when assessing patient experience before and after the comfort cart intervention [3]. Considering a power of 90% and a significance level of 5%, 132 patients will be required in each group (pre- and post-intervention), totaling 264 participants.

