**Table pone.0332773.t001:** 

Questions adapted from Lichen et al. (2021)			
* Question *		* Response options *	
*During your stay in the ED, what was your average comfort level?*		Very comfortable; Comfortable; Somewhat comfortable; Somewhat uncomfortable; Uncomfortable; Very uncomfortable	
*As a person in the emergency department, do you feel you were offered care specific to your individual needs (I.e. needs related to communication, hearing, vision, etc.)?*		Strongly agree; Somewhat agree; Neither agree nor disagree; Somewhat disagree; Strongly disagree	
Additional questions in the post-implementation phase			
*Did you use any of the items or services offered in the Geriatric Cart?*		Yes; No	
*Knowing that these items or services were available, even if I did not use them, made me feel more comfortable*		Strongly agree; Somewhat agree; Neither agree nor disagree; Somewhat disagree; Strongly disagree	
*The items I requested from the comfort cart made me feel more comfortable during my visit today*		Strongly agree; Somewhat agree; Neither agree nor disagree; Somewhat disagree; Strongly disagree	
*Having the comfort cart available improved my overall experience today*		Strongly agree; Somewhat agree; Neither agree nor disagree; Somewhat disagree; Strongly disagree	
*Having the comfort cart gave me more independence during my visit today*		Strongly agree; Somewhat agree; Neither agree nor disagree; Somewhat disagree; Strongly disagree	

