### Data management and statistical analysis

All study data will be collected and managed using Research Electronic Data Capture (REDCap) [30], a secure web-based application. Research assistants will use tablets with online access to the REDCap database for direct data entry and informed consent procedures.

For the primary objective evaluating the impact of the comfort menu and cart on the experience of older patients we will use the questionnaire adapted from Lichen et al. (2021) and McCusker et al. (2018). For the secondary objectives evaluating the impact of a comfort menu and cart on the experience of medical and multidisciplinary staff involved in caring for older patients treated in the ED, we will use the the questionnaire adapted from Lichen et al. (2021).

Data analysis will be performed using Stata version 17 (StataCorp, College Station, TX). All statistical tests will be two-tailed with an alpha error of 0.05. Numerical variables will be reported as means and standard deviations or medians and interquartile ranges (IQR) depending on their distribution, which will be assessed visually and using the D’Agostino-Pearson test for normality. Categorical variables will be described as absolute counts and proportions. Numerical variables will be compared using Student’s t-test or ANOVA for normal distributions and Wilcoxon or Kruskal-Wallis tests for non-normal distributions. As appropriate, categorical variables will be compared using the chi-square test or Fisher’s exact test. Analyses will be adjusted to account for potential confounding variables, such as baseline frailty, cognitive impairment, and clinical severity. Missing data will be handled though mixed effects model.

All relevant data from this study will be made available upon study completion.

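### The protocol points to three different measures as the primary outcome, and the stated 90% power belongs to only one of them

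*Protocol article*

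**What the plan says.** The primary objective names a construct and no variable: "Evaluate the impact of implementing a comfort menu and cart on the experience of older patients treated in the ED". Three later places bear on how that construct is measured.

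- **Sample size calculation.** The 132 per group (264 in total, 90% power, 5% significance) is based on a cited comfort-cart study with a "difference of 0.98 on a Likert scale (ranging from 1 to 6) when assessing patient experience before and after the comfort cart intervention".
- **Data management and statistical analysis.** "For the primary objective evaluating the impact of the comfort menu and cart on the experience of older patients we will use the questionnaire". Two sources are named: the comfort-cart study and an ED-experience questionnaire. The same section states: "All statistical tests will be two-tailed with an alpha error of 0.05".
- **Patient and public involvement.** "the primary patient experience outcome measures are adapted from the questionnaire developed by" the authors of the ED-experience questionnaire, that is, the second source.

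The items are listed under Initial interview. Two comfort-cart items are asked in both phases. One is average comfort, with six options ("Very comfortable; Comfortable; Somewhat comfortable; Somewhat uncomfortable; Uncomfortable; Very uncomfortable"); the other is care matched to individual needs, with five agreement options. Five further cart items are asked only after implementation. The ED-experience part has eight items, and each response is classed as a problem or no problem.

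**The concern.** The three places do not describe the same endpoint. The instrument called primary in the patient involvement section contains no 1-6 item, so it cannot yield the variable on which the trial was sized. The analysis section takes in both sources and so adds items of three different types.

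Two things are at stake. First, the Expected results section looks forward to demonstrating a positive impact. With no endpoint fixed, that claim could come to rest on whichever item turned out best. The design is an uncontrolled before-after comparison, so an endpoint fixed in advance is one of the few protections available. Second, the 90% power statement would be read as applying to the primary outcome, whichever measures that turns out to be.

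**Working it through.** **1. The plan's own figure.** For two means with equal groups, n = 2 × SD² × (1.960 + 1.282)² / 0.98². The article gives no SD, so 132 cannot be reproduced directly. Solving for the SD gives 0.98 / (3.2415 × √(2/132)) = 0.98 / 0.3990 = 2.46. The largest SD possible on a 1-6 scale is 2.5 (half the answers at 1, half at 6). Assumed SDs of 1.5 and 2.0 would need 50 and 88 per group. The missing SD is a separate matter. What counts here is that the calculation concerns a mean difference on a 1-6 scale and nothing else.

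**2. Which items fit which statement.**

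| Items asked in both phases | Type | Fits the sample-size scale | Covered by the analysis section | Covered by the patient involvement section |
|---|---|---|---|---|
| Average comfort (1) | 6 options | yes | yes | no |
| Individual needs (1) | 5 options | no | yes | no |
| ED-experience items (8) | problem / no problem | no | yes | yes |

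The count is 1 + 1 + 8 = 10. No item appears under all three statements. The five post-only cart items have no pre-intervention value and are not counted.

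**3. Error rate if ten items were tested separately and any one sufficed (a conditional calculation).** Under independence:

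- either direction: 1 − 0.95^10 = 0.401;
- favourable direction only, 0.025 per item: 1 − 0.975^10 = 0.224.

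The documents give no correlations between items. With ten equally correlated normal test statistics (400,000 simulated draws, cut-off 1.960):

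| Assumed correlation | At least one false positive, either direction | Favourable direction only |
|---|---|---|
| 0 | 40% | 22% |
| 0.3 | 35% | 18% |
| 0.5 | 29% | 14% |
| 0.7 | 21% | 11% |
| One named endpoint | 5% | 2.5% |

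**4. Power on a problem/no-problem item at 132 per group.** The documents give no problem rates, so all rates below are assumed. SE = √[(p1(1−p1) + p2(1−p2))/132], and power = Φ(|p1−p2|/SE − 1.960). For 40% to 25%: SE = √[(0.24 + 0.1875)/132] = 0.0569, 0.15/0.0569 = 2.636, and Φ(0.676) = 75%.

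| Assumed change in problem rate | Power |
|---|---|
| 10% to 5% | 34% |
| 30% to 20% | 47% |
| 20% to 10% | 63% |
| 40% to 25% | 75% |
| 50% to 30% | 92% |
| 40% to 20% | 95% |

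**The case against.** A reader might infer that the plan tests ten primary items, each at 0.05, and counts a positive result on any one as success. The document does not say so. It sets one alpha for all tests, and neither separate testing nor an any-item rule is written anywhere. Sorting answers into problem and no problem would suit a problem count as well as eight tests. Scoring and multiplicity rules are commonly left to a statistical analysis plan, which is not shown, so their absence from an article is no fault in itself. This stands, and it is why step 3 is conditional.

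The 40% figure also needs care. It assumes independence, which is implausible for answers from one respondent in one interview, and it counts false positives in both directions. For a false claim of benefit, the favourable-direction column applies. Fisher's exact test, which the plan permits, is conservative and would lower the figures further. Likewise, no single binary power figure is a property of the plan; only the range is informative.

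Finally, sizing a trial on one component of a two-source questionnaire is not a contradiction in itself, and the patient involvement section explains where the instruments came from without saying that only the second source is primary. That softens the conflict but does not remove it. Even if both sources are taken as primary throughout, the protocol names no variable, and the power statement covers one item of ten. An analysis plan could choose an endpoint, but no single endpoint would fit all three sections as they are worded.

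**Conclusion.** The point holds as a conflict within the protocol over its primary outcome. The sample size implies the 6-point comfort item, the analysis section names both questionnaires, and the patient involvement section calls the measures from the second source primary. That the sample size refers to the comfort item is itself an inference, but it is the only patient item with six options.

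The error rates (21-40% in either direction, 11-22% in the favourable direction) apply only if items are tested separately and any one can carry the claim, over assumed correlations from 0.7 to 0. The stated 90% power has no basis for the binary items: over the assumed rates it could be as low as about 34% or as high as about 95%.

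This should be settled before recruitment, which is planned to start in April 2026, because a choice made after data are seen would not protect the main conclusion.

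**What to change.** Name one primary endpoint and make the sections Sample size calculation, Data management and statistical analysis, and Patient and public involvement agree on it.

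- The choice that keeps the existing sample-size basis is the patient-rated 6-point comfort item, pre versus post, at two-sided 0.05. The SD behind 132 should be stated alongside it.
- A predefined score would also resolve the conflict, but it needs its scoring rule and its own power statement.
- With the comfort item as primary, make the other nine shared items secondary, either Holm-adjusted or labelled exploratory.
- Report the five post-only items descriptively. Nothing in the protocol proposes a before-after test of them, so this only makes their role explicit.

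With the comfort item, the cost is wording in three sections, with no change to data collection. The downside is that items other than the named endpoint can no longer carry the headline claim.

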### Ethics and dissemination

Ethical approval for this study has been granted by the Institutional Review Board of HSL (*Comitê de Ética em Pesquisa do Hospital Sírio Libanês/ Sociedade Beneficente de Senhoras*): certificate n^o^ 85870125.4.0000.5461, decision n^o^ 7.436.261, dated March 12 2025. All participants, or their legal representatives for those with cognitive impairment, will provide written informed consent before any study procedures are initiated.

Given that the study employs a quasi-experimental design, with no alteration to the participants’ clinical procedures, and includes participants both before and after the intervention, the informed consent form will not disclose details of the intervention in order to mitigate information bias. The purpose is to ensure that participants are unaware of the intervention studied, thereby preventing their perception of care from being affected by a perceived comfort, either absent or present, depending on their study phase.

The results will be shared with the academic community through peer-reviewed publications and presentations at relevant conferences to inform future clinical practice and research.

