#### Exclusion criteria.

Decline to participate in the study or use the comfort menu and cart.Absence of a companion able to consent to study participation and provide necessary information for patients with altered mental status or cognitive impairment.Decreased level of consciousness.Hemodynamic instability.Acute respiratory failure.Inability to be contacted by phone for the follow-up interview.

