### Intervention

The comfort menu and cart will be implemented after the pre-intervention data collection phase is completed. The menu will list the items available on the cart and will be presented to eligible patients in printed or digital format (on a tablet). The cart will be placed in an easily accessible area within the ED. Approximated retail prices have been previously reported [3].

A one-month dedicated rollout period will precede the commencement of post-intervention participant enrollment. This phase is designed for comprehensive staff training on the proper use and components of the comfort menu and cart, including familiarization with all available items and menu options. Additionally, this period will ensure all necessary equipment is adequately prepared and any potential logistical challenges associated with the cart’s implementation are identified and resolved, thereby optimizing the fidelity and effectiveness of the intervention before data collection for the post-intervention group begins.

Comfort Cart Contents:

Hot and cold packs;Extra blanket and pillow;Face towel;Gloves and hat;Personal hygiene kit (toothbrush, toothpaste, cotton swabs, sleep mask, comb, deodorant, hand lotion);Items for distraction (magazines, word search puzzles, playing cards, coloring pages);Items to enhance communication (reading glasses, magnifying glass, penlight, cell phone charger, notepad, sound amplification device).

Comfort Menu Options:

Physiotherapy assessment;Conversation with chaplain, concierge, or social worker;List of resources for older adults needing community services;Home care assistance.

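### Non-disclosure at consent can keep participants unaware of the intervention only in the pre-intervention phase, yet the protocol claims this protection of a self-rated primary outcome for both phases

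*Protocol article*

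**What the plan says.** Ethics and dissemination (Protocol article) describes one device for protecting patient ratings: "the informed consent form will not disclose details of the intervention in order to mitigate information bias". The aim is given as "The purpose is to ensure that participants are unaware of the intervention studied", and the claimed result is "thereby preventing their perception of care from being affected by a perceived comfort, either absent or present, depending on their study phase". The last words make this a claim about both phases. The same paragraph supports non-disclosure by describing the study as one "with no alteration to the participants’ clinical procedures".

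Other sections describe what a post-phase patient meets:

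- Intervention: the menu "will be presented to eligible patients in printed or digital format (on a tablet"). Its options include "Physiotherapy assessment;Conversation with chaplain, concierge, or social worker", and also home care assistance.
- Exclusion criteria: one criterion is "Decline to participate in the study or use the comfort menu and cart".
- Initial interview, first questionnaire table: post-phase patients answer extra items about the cart, such as "Having the comfort cart available improved my overall experience today".

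Data management and statistical analysis assigns both adapted patient questionnaires to the primary objective.

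**The concern.** The primary outcome is the patient's own rating of comfort and care, collected in the ED, and the comparison between phases is not randomised. If patients in one phase know about a new comfort service and patients in the other do not, some of the difference in ratings may come from courtesy towards those offering it, or from an expectation that it should help. Such effects can favour the post phase, and a larger sample does not remove them.

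An open intervention of this kind is acceptable if it is described as open. The difficulty is that the protocol says the bias is prevented in both phases. A reader who relies on that sentence would take the between-phase difference to be better protected than it is.

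**Working it through.** No figure in the protocol bears on this point, so the check sets the sections side by side.

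**Step 1. What the device can do in each phase.** The only device stated for participants is a consent form that omits details of the intervention.

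| | Pre phase | Post phase |
|---|---|---|
| Consent form gives details of the intervention | No | No |
| Menu presented | No, not yet implemented | Yes (Intervention) |
| Eligibility can turn on declining the cart | No, there is no cart to decline | Yes (Exclusion criteria) |
| Interview asks about the cart | No | Yes (Initial interview) |
| Patient can remain unaware | Yes | No |

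The last row follows from the rows above it. The claim in Ethics and dissemination covers both columns but is true of only one.

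**Step 2. Where the cart questions fall.** As printed, the post-phase patient questionnaire runs:

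1. Two common items: average comfort (six levels) and care specific to individual needs (five levels).
2. Five post-phase items about the cart and its contents. Four mention the cart by name, and four are positively worded agreement statements.
3. Eight common items on pain relief, respect, explanations, family access and discharge information.

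Groups 1 and 3 both serve the primary objective, so 2 + 8 = 10 common items. Two of the ten come before the cart questions and eight come after them. The section on patient and public involvement also describes the source questionnaire of group 3 as the origin of the primary experience measures. The article does not say that the printed order is the order of administration, but nothing in it prevents that.

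**Step 3. Whether another safeguard fills the gap.**

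- The only assessor described as blinded is the second research assistant, who makes the 30-day telephone call. That call does not collect the primary outcome.
- The Discussion accepts that self-report may bring information bias and offers validated instruments as mitigation. Validation does not make awareness equal between phases, and the Discussion does not say that the bias could fall on one phase.

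**Step 4. Size.** A constant reporting shift of b points in the post phase adds b to the difference in means, whatever the sample size. The protocol gives no information on b, and its design cannot separate b from the effect of knowing that help is available. No size is therefore derived.

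**The case against.** The strongest reply is that the consent device does real work. A pre-phase patient told that a comfort cart was coming might mark comfort down because it was missing, which would also favour the cart. Non-disclosure guards against that. This stands, so it would be wrong to infer that the claimed protection is absent altogether: it is present in one phase.

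The aim can also be read as keeping patients unaware that the cart is what the study tests. A patient can be shown a menu as part of ED care without knowing that, and the six-level comfort item is printed before any cart question, so those questions as printed cannot move it. This stands for the two items in group 1. It is weaker elsewhere, because eligibility is tied to the cart and eight common items follow the cart questions.

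Awareness is also partly the intervention. The questionnaire itself asks whether knowing that items were available brought comfort, and the primary objective concerns implementing the menu and cart. This stands too: only the courtesy and expectation component is bias.

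Three stronger readings are tempting but unsupported:

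- **The recruiting assistant hands out the menu and then asks about comfort.** The Intervention section names no one who presents it. It plans staff training on the cart, and a staff question asks about the work burden of offering such resources. Both point towards ED staff.
- **The bias has a particular size in points.** Any figure would be an assumption with no input from the document.
- **The menu plainly changes clinical procedures, or the ethics board was misinformed.** Most cart items are non-clinical, the document does not say whether the menu services are new to this ED, and the ethics submission is not shown.

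**Conclusion.** The point holds in a limited form. The statement that participants are kept unaware, and that perceived comfort is thereby prevented from affecting ratings whichever phase they are in, can be true only of the pre phase. In the post phase the menu, the exclusion criterion and the cart questions all contradict it. Neither the blinded 30-day caller nor the general caveat about self-report restores the protection.

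The direction of concern is towards the post phase. The size is unknown. The contradiction needs no assumption about it, and an awareness effect should not be counted wholly as bias. The point about question order assumes that items are asked in the order printed, which the article does not fix.

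The apparent conflict between unchanged clinical procedures and the services on the menu is minor: the two statements sit badly together and should be reconciled, but no alteration of care is established.

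**What to change.** 1. In Ethics and dissemination, limit the claim: participants are not told the study hypothesis, and those in the post phase are necessarily aware of the cart. In the Discussion, list awareness that differs between phases as a limitation, with its likely direction.
2. State that trained ED staff, not the interviewing research assistant, present the menu and supply items, independently of research screening.
3. Fix the interview order so that all ten common experience items come before any question about the cart.
4. As a minor point, reconcile the sentence on unaltered clinical procedures with the services listed on the menu.

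The cost is a few sentences, a reordered form and a line in the staff training already planned for the rollout month. Recruitment is scheduled to start in April 2026, so the changes should be settled before then. The downsides are small: the statement on bias becomes less favourable, and some patients may not be reached by staff.
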